## Abstract

**Background:**

Pregnancy presents a unique situation for the management of asthma as it can alter the course of asthma severity and its treatment, which in turn can affect pregnancy outcomes. Despite awareness of the substantial adverse effects associated with asthma during pregnancy, little has been done to improve its management and reduce associated perinatal morbidity and mortality. The aim of this randomized controlled trial is to evaluate the clinical and cost effectiveness of an Antenatal Asthma Management Service.

**Methods/design:**

*Design:* Multicentre, randomized controlled trial.

*Inclusion criteria:* Women with physician diagnosed asthma, which is not currently in remission, who are less than 20 weeks gestation with a singleton pregnancy and do not have a chronic medical condition.

*Trial entry and randomization:* Eligible women with asthma, stratified by treatment site, disease severity and parity, will be randomized into either the ‘Standard Care Group’ or the ‘Intervention Group’.

*Study groups:* Both groups will be followed prospectively throughout pregnancy. Women in the ‘Standard Care Group’ will receive routine obstetric care reflecting current clinical practice in Australian hospitals. Women in the ‘Intervention Group’ will receive additional care through the nurse-led Antenatal Asthma Management Service, based in the antenatal outpatient clinic. Women will receive asthma education with a full assessment of their asthma at 18, 24, 30 and 36 weeks gestation. Each antenatal visit will include a 60 min session where asthma management skills are assessed including: medication adherence and knowledge, inhaler device technique, recognition of asthma deterioration and possession of a written asthma action plan. Furthermore, subjects will receive education about asthma control and management skills including trigger avoidance and smoking cessation counseling when appropriate.

*Primary study outcome:* Asthma exacerbations during pregnancy.

*Sample size:* A sample size of 378 women will be sufficient to show an absolute reduction in asthma exacerbations during pregnancy of 20% (alpha 0.05 two-tailed, 90% power, 5% loss to follow-up).

**Discussion:**

The integration of an asthma education program within the antenatal clinic setting has the significant potential to improve the participation of pregnant women in the self-management of their asthma, reduce asthma exacerbations and improve perinatal health outcomes.

**Trial registration:**

ACTRN12613000244707

## Background

Pregnancy presents a unique situation for the management of asthma as it can alter the course of asthma severity and its treatment, which in turn can affect pregnancy outcomes. Despite awareness of the substantial adverse effects associated with asthma during pregnancy, little has been done to improve its management and reduce associated perinatal morbidity and mortality. Asthma is the most prevalent complication to affect human pregnancy in Australia, affecting an estimated 12% of pregnant women, or 36,000 pregnancies each year [1]. The significance of asthma in pregnancy is highlighted in a recent meta-analysis, demonstrating clear associations between asthma in pregnancy and adverse perinatal outcomes, including increased risk of low birth weight (RR 1.46; 1.22-1.75), small-for-gestational age (RR 1.22; 1.14-1.31), preterm delivery (RR 1.41; 1.22-1.61) and pre-eclampsia (RR 1.54; 1.32-1.81) [2]. The adverse effects of asthma in pregnancy are related to asthma severity and the intensity of treatment [3-5]. Studies of women with well controlled asthma, which involves the regular use of inhaled corticosteroids (ICS) to inhibit inflammatory mechanisms at a systemic level, seldom demonstrate adverse effects on fetal outcome [3,6]. In contrast, regular use of oral corticosteroids (OCS), used in the management of acute asthma exacerbations and poorly controlled asthma during pregnancy, has been associated with an increased incidence of low birth weight babies and preterm delivery [7]. A number of studies have examined the effects of maternal asthma during pregnancy, in the presence and absence of ICS treatment, on placental function and fetal development. These studies have demonstrated that use of ICS for the treatment of asthma did not affect fetal growth and that maternal asthma without treatment had a greater impact on the fetus and placenta [8]. Furthermore, acute asthma exacerbations were identified as the most significant event to affect fetal morbidity and mortality in pregnancies complicated by asthma [9,10]. That is, poor asthma control is a greater risk factor for an adverse outcome during pregnancy than ICS use [10]. In contrast, evidence demonstrates little or no increased risk of adverse maternal or fetal complications in situations where asthma is well controlled throughout pregnancy [6,11]. These findings point to the fact that optimization of asthma management and asthma control is key to improving perinatal outcomes. As such, pregnancy represents a significant indication to optimize therapy and maximize lung function in order to reduce the risk of acute exacerbation and resultant adverse health outcomes. This study will address these issues through the development and evaluation of cost effective ways of improving antenatal management of asthma.

### Current care of pregnant women with asthma

Clear guidelines exist for the management of asthma during pregnancy, which involves managing asthma medications in pregnant women in the same manner as a non-pregnant adult [12]. This relates to assessing asthma control and adjusting inhaled medications accordingly at regular intervals during pregnancy. The significant burden associated with asthma is highlighted through National Health Surveys which identified that approximately 12% of women of childbearing age report having current asthma [1,13]. While no studies have directly assessed the prevalence of asthma amongst pregnant women in Australia, prospective cohort studies [14] and antenatal surveys [15] undertaken amongst pregnant women have identified a similar prevalence of approximately 12-13%. Despite this estimated high prevalence, only 6% of pregnancies are reported to be affected by asthma in Australian perinatal statistics collections [16]. This apparent under reporting of asthma prevalence could be a result of the fact that asthma is not well recognized as a significant co-morbidity of pregnancy and has the potential to result in reduced capacity to manage the disease during pregnancy.

Currently, there is no structured approach in which asthma in pregnancy is managed. While a small number of women with very severe asthma receive monitoring during pregnancy in the antenatal clinic with respiratory physician support, treatment is often limited to women self-managing their asthma with support from their family doctor. Current asthma management appears to be focused on a reactive, rather than proactive, approach, which is demonstrated by the fact that only 15% of pregnant women with asthma involved in a prospective study had an asthma action plan [17]. Therefore, there is clear evidence that current care of pregnant asthmatic women could be significantly improved and there is an immediate need for evidence based approaches for improving clinical practice.

### Asthma exacerbations during pregnancy are associated with an adverse outcome

Exacerbations are a key feature of asthma and ideal target for improving asthma control and related outcomes. The definition of an asthma exacerbation is any asthma related event that involved one or more of the following; a hospital admission, an unscheduled doctor visit, a course of oral steroids or an increase in medication use. A systematic review identified that 6% of asthmatic women are hospitalized for a severe exacerbation during pregnancy, and that 20% have a severe exacerbation during pregnancy requiring medical intervention [7]. Furthermore, evidence demonstrates that the rates of exacerbations during pregnancy increases according to asthma severity [18]. Among those with mild, moderate and severe asthma the exacerbation rates have been reported as 13%, 26% and 52%, respectively [18]. The corresponding rates of exacerbations leading to hospitalization were 2%, 7% and 27% [18]. Relying solely on asthma severity, however, can be misleading as asthma can worsen during pregnancy regardless of maternal pre-pregnancy severity [7,10]. That is to say; an asthmatic woman can be a mild asthmatic pre-pregnancy and become a severe asthmatic during pregnancy. In addition, the severity of an exacerbation does not always reflect underlying asthma severity (i.e. women with mild asthma can have a severe exacerbation). This means it is difficult to identify accurately those women at risk of worsening asthma during pregnancy.

### Risk factors for exacerbations during pregnancy

While exacerbations can occur at any time during pregnancy, evidence from a prospective cohort of women with asthma identified that exacerbations were most likely in the second and third trimesters between weeks 17 and 34, with a peak incidence around 25 weeks gestation [10]. Risk factors associated with asthma exacerbations during pregnancy include respiratory viral infections and a lack of appropriate treatment with inhaled corticosteroids (ICS). Asthmatics appear to be more susceptible to respiratory tract infection during pregnancy and also have an increased risk of community-acquired pneumonia [19]. This suggests that the combination of asthma and pregnancy may significantly increase the risk of infection and may result in acute asthma exacerbations during pregnancy. Improvements in asthma management that address these issues and reduce exacerbation rates on a population basis are needed.

### Treatment of asthma and asthma exacerbations during pregnancy

Pregnancy has a unique effect on decisions around asthma control and management. Despite guidelines recommending the continuing of usual asthma medications during pregnancy, it is not uncommon for women to cease their medications, with or without consultation with their doctors [20]. These decisions may be driven by a perceived lack of need to continue their medications, a lack of support and guidance from health professionals regarding how to manage their asthma medications and/or concerns regarding the safety of asthma medications during pregnancy [21]. These concerns may not be unique to women themselves, as a previous survey demonstrated that in situations where asthma was well controlled, over 25% of family physicians would instruct their pregnant patients to decrease or discontinue asthma medication during pregnancy, despite the potential to negatively impact on subsequent asthma control [22]. Furthermore, a study conducted in the US found that pregnant women with an asthma exacerbation were significantly less likely to be given oral steroids either in the emergency department or on discharge from hospital than non-pregnant asthmatic women (50.8% vs. 72.4%) [23]. Subsequently, pregnant asthmatic women were three times more likely to report an on-going asthma exacerbation following discharge when compared with non-pregnant asthmatic women [23]. The lack of treatment of an exacerbation during pregnancy can severely compromise the fetus by reducing the oxygen supply to the utero-placental unit and has a more significant impact on the fetus than the medication itself [24]. Daily ICS use has previously been identified as a safe medical approach to controlling asthma during pregnancy and reducing the risk of exacerbation [24-27]. The uncertainty, concerns and variability in practice surrounding medication use and asthma control during pregnancy emphasizes the key need for a dedicated Antenatal Asthma Management Service.

### Existing evidence on the provision of asthma self-management skills and education during pregnancy

Previous research undertaken by the research team has demonstrated that asthma education combined with an asthma action plan administered in the antenatal clinic by a respiratory nurse is associated with a significant improvement in birth weight relative to women who did not use an action plan during pregnancy [17], and may reduce the risk of exacerbations as a result of improved asthma control.

In this study asthmatic women were prospectively recruited at their first antenatal visit and attended a nurse-led asthma management service at the antenatal clinic at 20 and 33 weeks gestation (n = 211) [17]. Lung function, asthma symptoms, compliance with medications, medication knowledge and inhaler technique were assessed. Women were given a written asthma action plan and educated in peak flow monitoring for home use. At the first visit, the majority of women were identified as having poor asthma self management skills and knowledge, regardless of the severity of their disease [17]. Limitations of this study were that the service was not assessed as part of a RCT (i.e. all women received intervention) and small sample size, limiting the ability to effectively assess the clinical and cost effectiveness of the intervention.

As a follow-up to this study a RCT was undertaken to investigate the clinical use of exhaled fraction of nitric oxide (F_E_NO), as a measure of inflammation, to adjust asthma management during pregnancy. Use of F_E_NO to adjust asthma treatment was associated with a significant reduction in the exacerbation rate during pregnancy (0.288 vs. 0.615; p = 0.001) and a reduction in neonatal hospitalizations (8% vs. 17%; p = 0.046) [28]. The major limitation of this trial, however, was that only non-smokers were enrolled in the study as cigarette use inhibits exhaled NO production in asthmatics and therefore can significantly mask the interpretation of NO data [29]. This significantly restricts the generalisability of this approach given the high proportion of asthmatic women who also smoke during pregnancy (reported to be at least 34% in one Australian cohort study) [14]. The applicability of F_E_NO to routine clinical settings is further limited due to issues around expense and accessibility. In addition, as all women in the study attended a respiratory nurse-led asthma management service, this limits the ability to adequately assess the clinical and cost effectiveness of this intervention.

While these two studies demonstrate the feasibility of providing an Asthma Management Service in the antenatal setting and the potential significant benefits it may achieve, an RCT is the only rigorous approach to truly determine the clinical and cost effectiveness of a nurse-led Antenatal Asthma Management Service versus standard clinical care.

### Summary

Given the scarcity of available health resources, the evaluation of the clinical and cost effectiveness of this intervention is important to establish whether our previous research findings can be translated into an effective clinical practice integrated with routine antenatal services. The proposed model makes use of specially trained respiratory nurses to deliver an Antenatal Asthma Management Service. The use of nurse-led clinics can facilitate specialist intervention at times of identified patient need, while nursing health practice allows for the introduction of preventative health practices to patients which cannot always be introduced by doctors due to limitations on time. The integration of an adapted model of an asthma education program within the antenatal clinic setting has the significant potential to improve the participation rate of pregnant women in the self-management of their asthma, reduce asthma exacerbations and thus improve perinatal health outcomes. It will also integrate well with a shared care model where asthma education occurs as part of the antenatal visits to the hospital with communication with the primary care physician and specialist physician. Positive outcomes will demonstrate the potential value of nurse led interventions, leading to closer consideration of other clinical conditions in which similar nurse-led initiatives could be evaluated and implemented.

### Aims and objectives of this trial

The aim of this randomized controlled trial is to evaluate the clinical and cost effectiveness of an Antenatal Asthma Management Service.

### Hypothesis

The provision of a nurse-led Antenatal Asthma Management Service (AAMS) is a cost effective intervention to improve asthma management and maternal health and well being and reduce the incidence of asthma exacerbations.

## Methods/design

### Ethics statement

Ethics approval was granted by the Human Research Ethics Committee of The Queen Elizabeth Hospital, Lyell McEwin Hospital and Modbury Hospital in Adelaide, South Australia (HREC/12/TQEHLMH/73).

### Study design

Multicentre parallel-group randomized controlled trial.

### Setting

This study will involve two public hospital antenatal clinics which account for 40% of all births in South Australia, Australia. These hospitals are the Lyell McEwin Hospital (LMH) and Flinders Medical Centre (FMC). A clinical study has been running at the LMH throughout 2012 to demonstrate the feasibility of implementing an Antenatal Asthma Management Service. During this period approximately 40 referrals have been received each month from the antenatal outpatient clinic for women with asthma. This represents an estimated prevalence of asthma in this population of 14%. This high prevalence is likely due to the fact that more than 70% of women with asthma use public health care and that the prevalence of asthma is higher among those with lower socioeconomic status [14], reflective of the area in which LMH is situated. In comparison to the LMH, FMC is situated in a region of higher SES than LMH (SA Health Atlas). This will enable the clinical and cost-effectiveness of the service to be investigated in two diverse settings, as previous research has identified that SES is a significant risk factor for outcomes related to maternal asthma [30].

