### Recruitment

All pregnant women with asthma attending their first booking visit (approximately 12 weeks gestation) at the antenatal outpatient clinic will be identified by the attending midwife. The midwife will ask several questions to establish the presence of asthma including “have you been told by a doctor that you have asthma? As well as “Have you used any asthma medications in the last year such as salbutamol or a preventer?” Women identified as having asthma will be referred by the attending midwife and will be subsequently interviewed by a research midwife associated with this study who will explain the project to them by providing both written and verbal information.

To be eligible, participants must be less than 20 weeks gestation at the time of recruitment, have asthma which has been previously diagnosed by a doctor and is not currently in remission (remission defined as no asthma symptoms and no use of asthma medications in previous year), aged 18–45 years, expected to give birth to a singleton and be able to speak English. Participants will be excluded from the study if they have previously participated in an Asthma study run at the hospital or have a pre-existing chronic medical condition (i.e. diabetes, hypertension, cardiac disease, HIV/hepatitis, renal disease, haematology disorder (i.e. thalassaemia, thrombophilia), thyroid disorder, psychiatric disease requiring therapy with antidepressant or antipsychotic, epilepsy).

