### Randomization

After the baseline assessment of asthma at 18 weeks gestation, women will be randomised to receive either standard care or nurse-led asthma management during pregnancy by contacting the central telephone randomization service at the University of Adelaide. The telephone randomization service will use a randomization schedule with balanced variable blocks, prepared by an investigator not involved with recruitment or clinical care. Stratification will be undertaken according to treatment site, parity and asthma severity. During the randomization call, eligibility will be checked and information collected to enable stratification and to assist in follow-up.

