### Sample size

In recognition of potential differences in the implementation and successfulness of the intervention across two distinct treatment sites, the sample size was calculated to ensure adequate statistical power within each treatment site. The total sample size of 378 pregnant women at baseline (189 in each group and each treatment site) was determined by power calculations (using 90% power and a 5% level of significance) using the primary outcomes of difference in exacerbation rate between treatment groups. We considered a 20% decrease (absolute reduction from 45% to 25%) in the incidence of asthma exacerbations as both achievable and clinically significant. The calculated sample size includes an estimated 15% loss to follow-up. We estimate there are at least 360 pregnancies complicated by asthma each year at each hospital and we will need to recruit 27% (n = 95 per site each year) of women presenting to the antenatal clinic per year to complete study recruitment over 2 years.

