### Statistical analysis

Baseline characteristics of all randomized women will be compared descriptively between the study groups. Outcome comparisons will be made according to the treatment allocation at randomization on an ‘intention to treat’ basis. For the primary outcome, the difference in exacerbation rates between groups will be compared using a Poisson regression model. This will enable calculation of the incident rate ratio and associated 95% confidence interval.

For secondary outcomes, discrete outcomes (i.e. low birth weight) will be analysed using log binomial regression and continuous outcomes (i.e. birth weight, gestational age) analysed using linear regression. Continuous variables with repeated measurements (i.e. questionnaire results, ACQ score) will be analysed using a generalized linear mixed model (GLMM) with a random intercept for individuals to account for repeated measurements.

Planned sub-analyses will be undertaken to assess the effects of asthma control, FEV1, asthma medication use, cumulative ICS exposure, asthma knowledge and medication adherence, on the primary and secondary outcomes. SPSS Version 20 (SPSS Inc., Chicago, IL, USA). and Stata IC 11.1 (Stata, College Station, TX, USA) will be used for analyses. Statistical significance will be assessed at the 0.05 level using a two-sided comparative test.

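### The trial is set up and sized to give results at each of two distinct sites, but the stated analysis names no site-specific estimate

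*Protocol article*

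**What the plan says.** Three parts of the protocol article treat site as something on which the trial will give an answer.

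- **Setting.** The two hospitals are chosen for contrast: "In comparison to the LMH, FMC is situated in a region of higher SES than LMH". The stated benefit is that "This will enable the clinical and cost-effectiveness of the service to be investigated in two diverse settings". The same section reports that "A clinical study has been running at the LMH throughout 2012 to demonstrate the feasibility of implementing an Antenatal Asthma Management Service". No counterpart at FMC is described.
- **Randomization.** "Stratification will be undertaken according to treatment site, parity and asthma severity".
- **Sample size.** The authors expect that implementation and success may differ by site, and for that reason "the sample size was calculated to ensure adequate statistical power within each treatment site". The numbers are given as "The total sample size of 378 pregnant women at baseline (189 in each group and each treatment site" and so on, that is, 189 women at each hospital.

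Two parts describe what will be computed.

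- **Statistical analysis.** The primary outcome is compared between randomised groups with a Poisson model. Sub-analyses are then listed: "Planned sub-analyses will be undertaken to assess the effects of asthma control, FEV1, asthma medication use, cumulative ICS exposure", followed by asthma knowledge and medication adherence. Site is not mentioned in the primary model or in this list.
- **Cost effectiveness.** Costs, QALYs, incremental ratios and net benefits are described by treatment group. No result by site is named.

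**The concern.** A stated aim and a sample-size rationale both rest on results at each site, but the analysis section, which does enumerate its sub-analyses, leaves site out. If the analysis is run as written, the trial gives one overall effect and nothing on whether the service worked in each setting.

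If site results are added after the data are seen, the form of comparison is open. The likely informal version is to set two separate p-values side by side, which is a poor way to judge whether effects differ. Any difference would also need careful reading, because the two hospitals are known to differ in more than one respect.

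**Working it through.** **1. The sections side by side.**

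| Section | Role of site |
|---|---|
| Setting | Reason for having two hospitals; covers clinical and cost-effectiveness |
| Randomization | Stratification factor |
| Sample size | Power intended within each site |
| Statistical analysis | Not mentioned in the primary model or the listed sub-analyses |
| Cost effectiveness | Not mentioned |

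The first three point to site-level estimates. The last two name none.

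**2. The plan's own figure.** Inputs from Sample size and Statistical analysis: 45% vs 25%, two-sided 5% level, 90% power, 15% loss, power within each site. With the pooled two-proportion formula,

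n per arm per site = [1.96·√(2·0.35·0.65) + 1.2816·√(0.45·0.55 + 0.25·0.75)]² / 0.20² = (1.3221 + 0.8453)² / 0.04 ≈ 117.4, so 118.

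That is 236 per site before loss. With 15% loss, 118/0.85 gives 139 per arm, so 278 per site and 556 in total. With the 5% loss given in the Abstract it is 250 per site and 500 in total. The stated 189 per site and 378 in total are not reproduced under these inputs. That is a separate matter and the present point does not depend on it. It is shown because the site-level power enters step 4.

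**3. Precision of the missing estimates.** With 189 per site and 1:1 allocation there are 94.5 per arm per site, or 89.8 after 5% loss and 80.3 after 15%.

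SE of one site's risk difference = √[(0.45·0.55 + 0.25·0.75)/n] = √(0.435/n). SE of the difference between the two sites' effects = √2 times that.

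| Loss | n per arm per site | Site effect, 95% half-width | Between-site contrast, 95% half-width | Contrast detectable at 80% power |
|---|---|---|---|---|
| 0% | 94.5 | 13.3 points | 18.8 points | 27 points |
| 5% | 89.8 | 13.6 points | 19.3 points | 28 points |
| 15% | 80.3 | 14.4 points | 20.4 points | 29 points |

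Take the extreme case of the full 20-point effect at one site and none at the other. Power for the contrast is about 55%, 53% and 48% with the SE above. If both arms at the no-effect site are at 45%, the SE becomes √[(0.435 + 0.495)/n] and power is about 52%, 50% and 46%. Either way it is roughly even odds.

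**4. Why separate site p-values are not a substitute.** Power within a site for 45% vs 25% is 82.7%, 80.7% and 76.2% at 0%, 5% and 15% loss. If the true effect is the same 20 points at both sites, the chance that exactly one site reaches significance is 2p(1−p):

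- 0% loss: 2·0.827·0.173 ≈ 29%
- 5% loss: 2·0.807·0.193 ≈ 31%
- 15% loss: 2·0.762·0.238 ≈ 36%

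About one trial in three would appear to show that the service works at one hospital only, when it works equally at both.

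**The case against.** The strongest reply is that this is a condensed article. Site-specific intervals and interaction terms are often left to a full protocol or SAP, and neither is shown. Stratifying by site and sizing within site show that a within-site comparison is intended. The analysis section does not say that the comparison is pooled only. The Cost effectiveness section says that it will establish in which circumstances the service is worthwhile, which leaves room for results by setting.

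Part of this stands: a fuller document may contain the analysis, so the claim must be confined to this one. It does not remove the mismatch. The article gives an aim and a sizing rationale built on site, then lists its sub-analyses and omits site.

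A reader might be tempted to go further in three ways, none of which the document supports.

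- **That the 2012 service at LMH has already changed standard care there.** Nothing says that midwives, GPs or usual practice changed, and no figure for carry-over is given. Women are protected in part by the rule that "Participants will be excluded from the study if they have previously participated in an Asthma study run at the hospital". Because allocation is stratified by site, the earlier service does not in itself bias the randomised comparison at LMH.
- **That the authors will read a site difference as a socioeconomic effect.** The text speaks of two diverse settings and never says that a difference will be attributed to socioeconomic status.
- **That individual socioeconomic status is not collected.** The article mentions a structured data collection form whose fields are not shown, so its silence proves nothing.

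**Conclusion.** The point holds as an internal mismatch. Setting, Randomization and Sample size prepare for results at each site, while Statistical analysis and Cost effectiveness name none. It is a gap in pre-specification and does not bias the overall randomised comparison.

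On the plan's own rates, the missing estimates would have 95% half-widths of about 13 to 14 points per site and 19 to 20 points for the contrast. These figures assume 45% and 25% at both sites, equal allocation within site and 0% to 15% loss. They are on the absolute scale on which the trial was sized, whereas the planned Poisson model gives a rate ratio. No precision can be given for cost-effectiveness by site, because the document states no variances for costs or QALYs.

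With one hospital in each socioeconomic setting, no contrast between the sites can separate socioeconomic status from anything else that differs between them. The 2012 feasibility service described only at LMH is one such difference. This limits interpretation and does not show that any carry-over occurred.

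**What to change.** In Statistical analysis, add that:

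1. site is included in the primary model, since it is already a stratification factor;
2. the treatment effect on exacerbations is reported for each site with a 95% confidence interval;
3. a treatment-by-site contrast is reported with its confidence interval and labelled exploratory, and the sites are not compared by their separate p-values.

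In Cost effectiveness, add that results are reported by site in the same way. State in the report that a feasibility service ran at LMH in 2012 as a known difference between the sites, and that a difference in effect between sites will not be attributed to socioeconomic status.

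The cost is a few sentences. Site is already recorded, and no extra patients, visits or data are needed. The downside is imprecision: at about ±19 to 20 points the contrast can reveal only very large differences between sites, and an inconclusive contrast must not be presented as evidence that the service works equally well at both.
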